##### Alzheimer’s Disease Assessment Scale-Cognitive-Plus

Change in global cognitive function will be measured by the ADAS-Cog-Plus using a multidimensional item response theory model, which utilizes item scores from multiple cognitive assessment instruments to generate a global cognitive function score and standard error of measurement for that score. The ADAS-Cog-Plus includes the original 13-item assessment of memory, language, and praxis [53] with additional measures of executive functions and verbal fluency. Executive functions are assessed using the: (1) Trail Making Test (parts A and B) [54], a measure of set-shifting; (2) verbal digit span forward and backward [55], a measure of working memory; (3) Digit Symbol Substitution Test [56], a measure of working memory and psychomotor speed; and (4) category fluency [57], a measure of semantic and working memory. Higher scores on the ADAS-Cog-Plus indicate poorer cognitive performance.

##### White matter hyperintensity quantification

Brain MRI scans will be acquired at baseline and trial completion (12 months) at the UBC MRI Research Center. Neuroimaging will be performed on a Philips 3.0-Tesla Achieva scanner (Best, The Netherlands) with an 8-channel phased array head coil. Three-dimensional (3D) T_2_-weighted (T_2_-w) and proton density-weighted (PD-w) structural MRI scans will be acquired to quantify WMH volume.

For detailed information on MRI sequence parameters, please refer to Table 1.

**Table 1 Tab1:** Magnetic resonance imaging protocol

	3D T_1_-w MPRAGE^a^	3D T_2_-w	PD-w	DWI^b^	GRASE	rs-fMRI
Resolution acquired/reconstructed (mm^2^)	1 × 1/1 × 1	1 × 1/0.8 × 0.8	0.99 × 1/0.98 × 0.98	2.24 × 2.24/2 × 2	0.99 × 2.04/0.96 × 0.95	3 × 3/3 × 3
Slice thickness acquired/reconstructed (mm)	1/1	1.6/0.8	1/1	2.20/2.20	5/2.5	3/3
Number of reconstructed slices	170	200	170	70	40	36
Field of view ap/rl/fh (mm)	256 × 200 × 170	256 × 160 × 256	250 × 170 × 250	224 × 224 × 154	230 × 190 × 100	240 × 240 × 143
Orientation	Transverse	Sagittal	Sagittal	Transverse	Transverse	Transverse
Echo time (ms)	3.5	363	30	60	8, 16, 24 … 384	30
Repetition time (ms)	1800	2500	3000	7.1	1073	2000
Flip angle (deg)	8	90	90	90	90	90
Acquisition time (min)	6:34	4:43	10:33	7:27	7:30	5:00
Purpose	Anatomical reference	WMH quantification	WMH quantification	White matter integrity quantification	Myelin quantification	Functional connectivity assessment

*ap* anterior-posterior, *rl* right left, *fh* foot-head

^a^Additional sequence parameters for 3D T_1_-w MPRAGE: inversion time = 810 ms

^b^Additional sequence parameters for DWI: 60 gradient directions at *b* = 700 s/mm^2^, 1 unweighted scan

T_2_-w and PD-w images will be preprocessed using standard and publicly available neuroimaging tools that include: (1) MR intensity inhomogeneity correction using a multiscale version of the nonparametric non-uniform intensity normalization method (N3) [58]; (2) a structure-preserving noise-removal filter (SUSAN) [59]; and (3) all non-brain tissues will be removed using the brain extraction tool (BET) [60].

WMHs will then be identified and digitally marked by a radiologist/neurologist with experience in WMH identification. The radiologist/neurologist will be blinded to all participant information, including treatment assignment. Baseline and 12-month scans will be co-registered and reviewed together to ensure consistency of identification of small lesions across time. The radiologist/neurologist will use the following guidelines in the seeding procedure, which was designed to be efficient and intuitive: (1) mark all distinct WMH regardless of size; (2) place more than one point on a lesion if the additional points would help define the extent of the lesion; and (3) place at least one point near the center of each lesion [61].

The seeded images will then be segmented by a method that automatically computes the extent of each marked lesion to create a lesion mask [61]. This segmentation method has been validated in large data sets with a wide range of lesion loads. It was found to be highly accurate compared to manual radiologist segmentations and also robust to variations in the placement of seed points [61]. Full details on the point placement procedure and subsequent automatic segmentation are described in previous work [61]. The lesion masks were then used to quantify WMH volume in cubic millimeters (mm^3^). All lesion masks will be reviewed by a trained research assistant to ensure accuracy.

#### Secondary outcomes

##### Brain magnetic resonance imaging

In addition to WMH volume, measures of brain structure and function will be acquired. Following a survey and reference scan, the following sequences will be collected: (1) 3D T_1_-weighted (T_1_-w) with an inversion recovery magnetization-prepared rapid acquisition with gradient echo (MPRAGE) sequence for anatomical reference; (2) diffusion-weighted imaging (DWI) acquired with high angular resolution to quantify white matter integrity; and (3) whole-brain 48-echo gradient and spin echo (GRASE) for T_2_ measurement to quantify myelin [62].

In addition, a subset of participants will also undergo an 8-min resting-state functional MRI (rs-fMRI) to assess changes in the connectivity of large-scale functional networks. During this scan, participants will be asked to rest with their eyes open while looking at a fixed point and to think of nothing in particular. The rs-fMRI scan will be used to establish the relevance of lesion location on changes in functional connectivity, in conjunction with a technique called lesion network mapping [63, 64]. Within this technique, the location of each WMH will be overlaid onto the functional connectivity of a human connectome. This will identify the level of overlap between the functional connectivity associated with the location of the WMHs and that of the large-scale functional networks. For detailed information on MRI sequence parameters, please refer to Table 1.

##### Cognitive function

The ADAS-Cog-13 is a 13-item assessment of memory, language, and praxis [53]. Scores range from 0 to 85, with higher scores indicating greater cognitive impairment. Three key executive processes will be assessed: (1) set-shifting; (2) working memory; and (3) selective attention and conflict resolution. We will measure set-shifting using the Trail Making Test (parts A and B) [54]. Working memory will be assessed by the verbal digit span forward and backward tests [57]. The Digit Symbol Substitution Test will measure psychomotor speed and working memory. The Stroop Color-Word Test [65] will measure selective attention and conflict resolution. The Picture Sequence Memory Test from the National Institute of Health Toolbox [66] will measure episodic memory. Participants will see a sequence of pictured activities presented in a specific order and are asked to put the pictures back into the order that was demonstrated. At practice, participants will be presented with four pictures, and for the main task, they will be presented with a sequence of 12 and then 16 pictures.

##### Physical performance

**Balance and mobility**

The Short Physical Performance Battery [67] includes standing balance (i.e., side-by-side stand, semi-tandem stand, and tandem stand), 4-m walk test, and repeated chair stands. Each component is rated from 0 (inability to perform the task) to 4 (optimal performance), for a maximum of 12 points. A score < 9 is predictive of subsequent disability [67].

**Functional mobility**

The Timed-Up-and-Go (TUG) test is a timed assessment that requires participants to stand up from a chair, walk 3 m at their usual speed, turn, walk back to the chair, and sit back down [68]. We will assess performance on the standard TUG test and on a dual-TUG test, whereby participants will be asked to subtract sevens from a randomly given number, while performing the task [68, 69]. A subset of participants will also complete a dual-task walking assessment. Using a GAITRite mat [70], participants will be asked to: (1) name as many items from a given category (category fluency) in 30 s while standing; (2) walk at their usual pace along the mat; and (3) walk at their usual pace while completing the category fluency task. Dual-task cost is calculated as (dual-task time − walking time)/walking time. A lower score is indicative of better dual-task performance.

**Physiological fall risk**

We will use the Physiological Profile Assessment© (PPA) [71] to assess physiological fall risk. The PPA has a 75% predictive accuracy for falls in older adults [71]. It is composed of five physiological domains: (1) postural sway, (2) hand reaction time, (3) dominant quadriceps strength, (4) proprioception, and (5) edge contrast sensitivity. A PPA *z*-score of 0–1 is indicative of mild fall risk, 1–2 indicates moderate risk, 2–3 indicates high risk, and > 3 indicates marked risk.

**Functional capacity**

We will assess functional capacity using the six-minute walk test [72]. Participants will be asked to walk as far as they can in 6 min, breaks included. We will record blood pressure immediately before and after the walk, and participants will be asked to rate their walk on the Borg Rating of Perceived Exertion scale [73]. Performance will be recorded as the number of meters walked in 6 min.

**Muscular strength**

We will assess upper body strength using maximal hand grip strength measured by a dynamometer. For the lower body, we will measure dominant quadriceps (isometric) strength using a simple strain gauge to the nearest 0.5 kg. In a subset of participants, lower body strength will be assessed using a Biodex System 4 Pro™ dynamometer. Maximal torque at a velocity of 60°/s and 180°/s will be recorded for both knee flexion and extension.

##### Cardiometabolic risk factors

We will assess: (1) resting systolic and diastolic blood pressure; (2) blood biomarkers (e.g., serum glucose and lipid profile), collected from fasted blood samples; (3) body mass index (BMI), using the formula mass (kg)/(height (m)^2^); (4) waist-to-hip ratio, by measuring hip and waist circumference in centimeters; and (5) arterial stiffness as measured by carotid-femoral pulse-wave velocity using the Complior system (Alam Medical, France).

##### Sleep and physical activity

Subjective sleep quality will be measured by the Pittsburgh Sleep Quality Index, a self-rated questionnaire assessing sleep disturbances over a 1-month period [74]. Objective measures of sleep quality will be estimated over a 2-week period using the MotionWatch8© (MW8) wrist-worn actigraphy unit (CamNtech; Cambridge, UK) to estimate sleep duration, latency, and fragmentation. Participants will also be asked to complete the Consensus Sleep Diary each morning [75]. In addition to sleep quality, the MW8 will also be used to calculate daily physical activity. The number of minutes spent in moderate to vigorous physical activity (> 3.0 METs) is compared to the total time spent awake and out of bed to determine the percentage of each day spent in physical activity [76].

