## Methods

### Design

We will conduct a 12-month, parallel group, proof-of-concept RCT of 88 community-dwelling adults with SIVCI, aged 55 years and older. Participants will be randomly assigned to receive 12 months of (1) twice-weekly PRT or (2) twice-weekly balance and tone training (BAT; active control). There will be three measurement points occurring at baseline, 6 months, and 12 months conducted by blinded assessors (Fig. 1). The experienced research team will implement standardized protocols and train study personnel (Fig. 2).

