#### Treatment allocation

##### Randomization

Participants will be randomly assigned (1:1) to either the 12-month, twice-weekly PRT program or the 12-month, twice-weekly BAT program. The randomization sequence will be generated and held by a central web-based randomization service. Permuted blocks of varying sizes will be used to ensure balance over time.

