#### Experimental groups

All classes will be led by certified instructors with a participant to instructor ratio of 4:1. Each 60-min class will include a 10-min warm up (i.e., stretching of the major muscles and walking on the spot), 40-min of training, and a 10-min cool down (i.e., stretching and relaxation techniques). Every instructor will be audited on a monthly basis by the exercise class coordinator to ensure consistent protocol delivery.

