##### Progressive resistance training

The PRT program will consist of a combination of free weight exercises including mini-squats, mini-lunges, and lunge walks and pressurized air system exercises including biceps curls, seated row, latissimus dorsi pull downs, triceps extension, leg press, hamstring curls, and calf raises. The intensity of training will begin at 50–60% of their 1 repetition maximum (1RM) and progress to 2 sets of 6–8 repetitions at 75–85% 1RM by week 4. The 7RM method will be used to increase the training load when 2 sets of 6–8 repetitions are completed with the correct form. The number of sets completed and the load lifted will be recorded for each participant at each class.

To meet the public health mandates of COVID-19, when it is necessary, training will occur at home, with the use of resistance bands of various weights. Participants will be provided access to instructional videos by either YouTube or DVD. They will be called on a weekly basis to monitor progress and compliance.

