##### Balance and tone training

The BAT program will consist of stretching, basic core/kegal exercises, deep breathing, and relaxation techniques. Other than body weight, no additional loading will be applied to any of the exercises. This training has not been shown to improve cognitive function [82] and thus will serve as a control for confounding variables such as physical training received by traveling to the training centers, social interaction, and changes in lifestyle secondary to study participation.

To meet the public health mandates of COVID-19, when it is necessary, training will occur at home, with the use of small equipment (e.g., Pilate ball). Participants will be provided access to instructional videos by either YouTube or DVD. They will be called on a weekly basis to monitor progress and compliance.

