#### Intervention compliance

Class attendance will be recorded by the instructors and compliance will be defined as the percentage of the total classes attended. To promote adherence to the exercise program, we will implement strategies including: (1) regular contact; (2) developing coping and action plans; (3) setting implementation intentions and concrete plans; and (4) encouraging participants to self-monitor their progress. Monthly monitoring of extracurricular physical activities will also be performed by an unblinded assessor using the Physical Activities for the Elderly [83, 84] questionnaire throughout the study. In addition, at each measurement point, physical activity over 14 days will be quantified using data acquired by the MW8 [76].

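### The MW8 physical activity outcome makes no allowance for trial sessions, so a 6-month PRT–BAT difference could reflect the assigned class rather than changed daily behaviour

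*Protocol article*

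**What the plan says.** Physical activity is among the secondary objectives listed at the end of the Introduction. Under Sleep and physical activity, the MW8 measure takes waking time out of bed as its denominator: "The number of minutes spent in moderate to vigorous physical activity (> 3.0 METs) is compared to the total time spent awake and out of" (…). The result is a percentage of each day. Intervention compliance adds that "at each measurement point, physical activity over 14 days will be quantified using data acquired by the MW8".

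On timing, the Design section says "There will be three measurement points occurring at baseline, 6 months, and 12 months". Allocation concealment places randomization after the baseline assessments. Under Randomization, "Participants will be randomly assigned (1:1) to either the 12-month, twice-weekly PRT program or the 12-month, twice-weekly BAT program".

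On class content, Experimental groups says "Each 60-min class will include a 10-min warm up", followed by 40 minutes of training and a 10-minute cool-down, for all classes. PRT participants "progress to 2 sets of 6–8 repetitions at 75–85% 1RM by week 4". For the control arm, "The BAT program will consist of stretching, basic core/kegal exercises, deep breathing, and relaxation techniques", and "Other than body weight, no additional loading will be applied to any of the exercises".

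Statistical analyses applies one mixed model, with group, time (6 and 12 months) and their interaction, to primary and secondary outcomes alike.

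**The concern.** Class time is time spent awake and out of bed. Read literally, the definition puts it in the denominator, and puts any class minute above 3.0 METs in the numerator. Baseline recordings contain no trial classes; 6-month recordings do. Loaded squats, lunges and machine work may well register differently from stretching, breathing and relaxation. Baseline adjustment cannot remove a difference that the assigned class creates after randomization.

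Two conclusions are at stake. The trial could report that PRT raises daily physical activity when participants only attended their sessions. It could also miss a compensatory fall in activity outside class, because class minutes would offset it.

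**Working it through.** The protocol gives no figure for this effect, so there is none to reproduce. The check is a bound built from the protocol's own schedule.

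**Inputs from the protocol article**
- Recording window: 14 days (Intervention compliance).
- Class frequency: 2 per week in both arms for 12 months (Randomization).
- Class structure: 10 min warm-up, 40 min training, 10 min cool-down in both arms (Experimental groups).
- Attendance: 100%, or the 60% compliance threshold (Statistical analyses).

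**Assumptions not in the documents**
- Time awake and out of bed: 14 to 16 h/day.
- Equal attendance in the two arms.
- For the bound, every PRT training minute and no BAT training minute exceeds 3.0 METs at the wrist.

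**Step 1. Classes in the window.** 2 per week × 2 weeks = 4.

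**Step 2. Minutes that can differ by arm.** Warm-up and cool-down are the same in both arms, so with equal attendance they cancel. That leaves the training block:
- 100% attendance: 4 × 40 = 160 min; 160 / 14 = 11.4 min/day.
- 60% attendance: 160 × 0.6 = 96 min; 96 / 14 = 6.9 min/day.

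**Step 3. Effect on the outcome, in percentage points** = minutes per day / (waking hours × 60) × 100.

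| Attendance | 14 h waking day | 16 h waking day |
|---|---|---|
| 100% | 11.43 / 840 = 1.36 | 11.43 / 960 = 1.19 |
| 60% | 6.86 / 840 = 0.82 | 6.86 / 960 = 0.71 |

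**Step 4. Could a gap of that size matter?** The documents give no SD for this outcome. The table takes assumed SDs of 20, 30 and 40 min/day and the 35 per arm left after the planned drop-out (two-sided alpha 0.05). It shows the standardised difference and the chance that the artefact alone would reach significance.

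| Assumed SD (min/day) | 100% attendance: d, power | 60% attendance: d, power |
|---|---|---|
| 20 | 0.57, 0.67 | 0.34, 0.30 |
| 30 | 0.38, 0.36 | 0.23, 0.16 |
| 40 | 0.29, 0.22 | 0.17, 0.11 |

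**Step 5. After the change.** With class intervals removed from numerator and denominator, the direct class contribution is zero in both arms by construction. Recording time lost at full attendance is 4 × 60 = 240 min. That is 240 / (14 × 960) = 1.8% of waking time at 16 h, or 240 / (14 × 840) = 2.0% at 14 h.

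**The case against.** The strongest reply is that the protocol describes this measure as daily physical activity and never as activity outside the programme. On that construct, counting class minutes is correct: if PRT adds moderate-to-vigorous minutes, total activity did rise. This stands, and it is why total activity should be kept. It does not tell a reader whether behaviour outside class changed, and the definition as written cannot separate the two.

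A second reply is that masking class intervals is a processing rule that an article may leave to the full protocol. It is true that the article does not positively say that the device is worn in class or that class minutes are kept. But its definition refers to all time awake and out of bed, and an unstated exclusion would change what the outcome means.

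Four stronger readings are tempting, and the documents do not support them.
- *The check on outside activity is contaminated.* The named check under Intervention compliance is the monthly questionnaire on extracurricular activity. It does not depend on the MW8, which is added as a separate measure of physical activity. The MW8 misleads only if read as outside activity.
- *Attribution of a cognitive or WMH effect is undermined.* The primary comparison is randomized and by intention to treat, and MW8 activity is not stated to enter it.
- *The gap could reach 240 minutes per fortnight (17.1 min/day).* That counts the warm-up and cool-down, which both arms share.
- *The group-by-time term is distorted.* This would follow if the 12-month recording came after the last class, which the protocol does not state.

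**Conclusion.** The point holds for one secondary outcome. Followed as written, the plan allows the assigned class itself to create a PRT–BAT difference in MW8 activity at 6 months, and the MW8 data cannot serve as an objective measure of activity outside the programme.

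The bound on the gap is 11.4 min/day (about 1.2 to 1.4 percentage points) at full attendance and 6.9 min/day (about 0.7 to 0.8 points) at 60% attendance. It rests on the assumed waking day, on equal attendance, and on the extreme assumption that all PRT training and no BAT training registers above 3.0 METs. Rest between sets and incomplete capture of resistance work at the wrist would make the real gap smaller. The documents do not say how the device scores either class, so the true size cannot be determined. The assumed SDs show only that the artefact could be large enough to matter. This is a low-cost improvement to what the outcome can show, not a threat to the trial's main conclusions.

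**What to change.** 1. Keep moderate-to-vigorous activity over the whole recording, labelled as including trial sessions.
2. Add the same measure with scheduled class intervals removed from numerator and denominator, by one rule applied identically in both arms at 6 and 12 months. Base conclusions about daily behaviour outside the programme on this version.
3. Where session times cannot be recovered, as may be so for past home sessions, exclude the known session days or flag the recording.
4. State whether the 12-month recording falls before or after the last class.

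The cost is some data processing and some lost recording time: about 2% of waking time if only class intervals are removed, or 4 of 14 days if whole session days must be dropped. Instructors already record attendance, but the article mentions no clock times, so these must be retrieved from class schedules. Home sessions still to come need a logged time during the recording fortnight. No extra visit or participant is needed.

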##### Mood and quality of life

Mood will be measured using the Centre for Epidemiologic Studies Depression Scale [77], which is a 20-part questionnaire that asks how often over the past week symptoms associated with depression were experienced. It is scored out of 60 with higher scores indicative of greater depressive symptoms. The ICEpop CAPability Measure for Older adults [78, 79] will be used to assess wellbeing across five attributes: (1) attachment (love and friendship); (2) security (thinking about the future without concern); (3) role (doing things that make you feel valued); (4) enjoyment (enjoyment and pleasure); and (5) control (independence).

